As a sensitivity analysis, hemodynamic and respiratory parameters will be assessed at prespecified time points to evaluate temporal changes and validate consistency with the primary outcome. Measurements will be obtained before induction (T0); every minute for 10 min from induction drug initiation (T1–T10); every 10 min for 30 min after establishment of both the Trendelenburg position and pneumoperitoneum (T20–T23); at pneumoperitoneum release (T30) and 10 min afterward (T31); and upon PACU arrival (T40), followed by every 10 min for 30 min (T41–T43). Arterial blood gas analysis will be performed at T10, T21, and T31. During anesthesia induction and maintenance, HR, SBP, diastolic blood pressure (DBP), MAP, respiratory rate (RR), SpO_2_, ETCO_2_, cardiac output (CO), cardiac index (CI), and stroke volume variation (SVV) will be recorded. In the PACU, HR, SBP, DBP, MAP, RR, and SpO_2_ will be recorded at the same prespecified intervals.

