### Sample size

2.7

A previous study reported the median and interquartile range of intraoperative MAP during total intravenous anesthesia in patients receiving remimazolam or propofol (remimazolam: 81.3 [76.9–92.5] mmHg; propofol: 76.8 [67.8–82.5] mmHg) (Tsukimoto et al., 2024). Based on these findings, we will estimate the means and standard deviations using the method described by Wan et al. (2014). The required sample size was calculated using G*Power software (version 3.1; Heinrich Heine University, Düsseldorf, Germany). With 80% power and a two-sided significance level of 0.05, 26 participants per group are required (effect size = 0.7). To account for a 10% dropout rate, we will recruit a total of 58 patients.

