### Statistical analysis

2.11

The primary outcome, TWA-MAP, will be analyzed using analysis of covariance, with group assignment as the fixed factor and baseline MAP, age, BMI, ASA-PS, and histories of hypertension and diabetes as covariates. Secondary outcomes, including hypertensive and hypotensive burden (area under the curve above or below predefined thresholds), will be compared between groups using Student’s t-test for normally distributed variables or the Mann–Whitney U test for non-normally distributed variables. Categorical outcomes, such as intraoperative hypotension, hypertension, bradycardia, tachycardia, PONV, and postoperative analgesic use, will be evaluated using the chi-square test or Fisher’s exact test, as appropriate.

Repeated-measures variables across prespecified time points (T0–T43), including HR, SBP, DBP, MAP, CO, CI, SVV, ETCO_2_, and arterial blood gas parameters, will be analyzed using generalized estimating equations (GEE) to assess group, time, and group-by-time interaction effects. An appropriate working correlation structure will be selected to account for within-subject correlations over time. As a sensitivity analysis, GEE analysis of serial blood pressure data will be performed to evaluate consistency with findings from the primary TWA-MAP analysis.

The primary efficacy analysis will follow the per-protocol (PP) principle, including all randomized participants who fully adhere to the study protocol. Participants with major protocol deviations, such as conversion to open surgery, administration of inhalational anesthetics, incomplete intraoperative hemodynamic monitoring, or early withdrawal, will be excluded from the PP analysis. Participants who discontinue the intervention due to serious adverse events will also be excluded. No intention-to-treat analysis is planned. The safety population will include all participants who receive at least one dose of the assigned anesthetic agent and will be analyzed according to the treatment actually administered.

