Missing data will be minimized through prospective monitoring of CRFs. For continuous outcomes, if ≤ 5% values are missing, linear interpolation will be performed; if > 5% are missing, the participant will be excluded from the PP analysis. For repeated-measures outcomes, non-parametric generalized estimating equations will accommodate incomplete time series, allowing valid population-level inference. For categorical variables, missing values will be reported explicitly, and sensitivity analyses will be conducted to evaluate their potential influence on study findings.

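### If the GEE group-by-time interaction is run as the usual uncorrected sandwich Wald test over all time points, its type I error is about 55% for blood pressure and heart rate, not 5%

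*Protocol article*

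**What the plan says.** Section 2.11 (Statistical analysis) covers HR, SBP, DBP, MAP, CO, CI, SVV, ETCO2 and arterial blood gases over T0–T43. These "will be analyzed using generalized estimating equations (GEE) to assess group, time, and group-by-time interaction effects". The working correlation is to be chosen as appropriate. The article names no variance estimator, test statistic, reference distribution, small-sample correction or coding of time. GEE of serial blood pressure is also the sensitivity analysis for the primary TWA-MAP result.

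Section 2.6 (Outcomes) sets the schedule: T0, then "every minute for 10 min from induction drug initiation (T1–T10"), then T20–T23, T30–T31 and T40–T43. In the PACU only HR, SBP, DBP, MAP, RR and SpO2 are recorded. Blood gases are taken at T10, T21 and T31.

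Section 2.7 (Sample size) states that "26 participants per group are required (effect size = 0.7") and that "we will recruit a total of 58 patients".

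On missing data, section 2.11 asserts that "non-parametric generalized estimating equations will accommodate incomplete time series, allowing valid population-level inference".

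**The concern.** The schedule is irregular and tied to surgical events, so time is most naturally a category. The interaction then has 20 degrees of freedom for variables with 21 points, and its covariance is estimated from about 52 patients. The sandwich estimator and its chi-square reference are large-sample tools. With 20 contrasts and 52 clusters, the Wald statistic is far too large under the null.

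The group-by-time term is the planned test of whether trajectories differ between the drugs. If it rejects a true null about half the time, a significant interaction in MAP or HR says almost nothing, and it cannot serve as a check on the primary result.

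The missing-data sentence adds a separate wording problem. GEE is semiparametric, because it needs a specified mean model. Unweighted GEE on incomplete series is in general valid only if data are missing completely at random, and the sentence sets no such condition.

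**Working it through.** **The plan's own figures.** The article states no error rate for the GEE tests, so there is none to reproduce. For the sample size, 52/(1 − 0.10) = 57.8, which rounds up to the stated 58. I take 26 per arm as the number analysed and 29 per arm as the upper bound. Whether 26 follows from the stated effect size is a separate question and does not enter here.

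**Time points (section 2.6).**
- HR, SBP, DBP, MAP: 1 + 10 + 4 + 2 + 4 = 21, so p = 20 interaction df.
- CO, CI, SVV, ETCO2 (no PACU values; T0 assumed recorded): 1 + 10 + 4 + 2 = 17, so p = 16.
- Blood gases: 3, so p = 2.

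**Formula.** Let n be patients per arm and N = 2n. With complete data and a saturated group-by-time mean model, the GEE estimates are the cell means whatever common working correlation is used. The uncorrected sandwich variance of an arm mean is (n − 1)S/n² instead of S/n. The Wald statistic is therefore W = T² × n/(n − 1), where T² is Hotelling's statistic. Under the null, T² × (N − p − 1)/[(N − 2)p] follows F(p, N − p − 1). The true size is

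P{ F(p, N − p − 1) > χ²₀.₉₅(p) × [(n − 1)/n] × (N − p − 1)/[(N − 2)p] }.

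**n = 26, N = 52.**
- p = 20: 31.41 × 25/26 × 31/(50 × 20) = 0.936; P(F(20,31) > 0.936) = 0.552.
- p = 16: 26.30 × 25/26 × 35/(50 × 16) = 1.106; P(F(16,35) > 1.106) = 0.386.
- p = 2: 5.991 × 25/26 × 49/(50 × 2) = 2.823; P(F(2,49) > 2.823) = 0.069.
- Overall group effect, p = 1: 3.841 × 25/26 = 3.694; P(F(1,50) > 3.694) = 0.060.

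**n = 29, N = 58.** The same formula gives 0.482, 0.337 and 0.067 for p = 20, 16 and 2.

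**Simulation under the null, nominal 5%.**

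| Scenario | Rejections |
|---|---|
| 21 points, 26/26, exchangeable data (5,000 runs) | 54.4% |
| 21 points, 26/26, AR(1) data (5,000 runs) | 54.9% |
| 21 points, arms 24/28 and 22/30 (5,000 runs each) | 56.8% and 58.5% |
| 17 points, 26/26 (5,000 runs) | 38.0% |
| 3 points, 26/26 (5,000 runs) | 6.8% |
| GEE fits, 21 points: exchangeable / independence working correlation (600 each) | 53.7% / 55.2% |
| GEE fits, 21 points, exchangeable, 3% of values missing (600) | 56.3% |

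**Candidate remedies, N = 52.**
- Bias-corrected (Mancl–DeRouen) sandwich with chi-square, 20 df. W becomes T² × 25/26, and 31.41 × 26/25 × 31/1000 = 1.013, so the size is 0.476. GEE fits gave 48.7%.
- The same sandwich with F(20,50), 20 df. The bound is 20 × 1.784 = 35.68, and 35.68 × 26/25 × 31/1000 = 1.150, so the size is 0.355.
- Hotelling-type F(20,31), 20 df: 4.9% in simulation.
- Four phases (3 df), uncorrected, chi-square: 7.815 × 25/26 × 48/150 = 2.405; P(F(3,48) > 2.405) = 0.079.
- Four phases (3 df), bias-corrected, F(3,50): 3 × 2.790 × 26/25 × 48/150 = 2.786; P(F(3,48) > 2.786) = 0.051.

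**The case against.** The strongest objection is that these error rates belong to a test the article does not name. Details of this kind are commonly left to an analysis plan, which is not shown here, and the answer depends on them. On the same data a Hotelling F reference rejects 4.9%, a score test about 1.6%, and a 1-df linear-time interaction about 6%. This stands. A reader might infer that the trial has committed itself to a test with a 55% error rate, but the document does not support that. The figures are conditional on categorical time and the uncorrected Wald chi-square.

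A reader might also infer that about half of all the listed variables would be falsely significant. Only HR, SBP, DBP and MAP of the eight named vital-sign and flow variables have 21 points. The other four are near 39%, and blood gases near 7%.

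Nor do the trial's main conclusions rest on this test. The primary outcome is TWA-MAP by ANCOVA, and the burden outcomes use a t-test or Mann–Whitney test. GEE of serial blood pressure is labelled a sensitivity analysis, and its most direct counterpart to TWA-MAP is the 1-df group effect. The discussion also asks for caution with secondary and exploratory results.

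On missing data, participants with more than 5% missing values are excluded from the per-protocol analysis. Little missingness is therefore expected, and no bias has been quantified. The validity claim there concerns incomplete series, not small-sample test size.

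What remains is that the document fixes the schedule, the sample size and a GEE interaction test. Run in its ordinary form, that combination fails, and the only technical safeguard mentioned, the working correlation, does not help.

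**Conclusion.** The point holds in conditional form. With categorical time and the uncorrected sandwich Wald chi-square test, the group-by-time interaction has a true type I error of about 55%, 39% and 7% for 21, 17 and 3 time points at 26 per arm, and 48%, 34% and 7% at 29 per arm. The formula assumes complete, normally distributed data, equal arms and a common covariance. Simulation with unequal arms or 3% missing values gave slightly higher figures.

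The effect is limited to secondary and sensitivity claims that trajectories differ. The overall group effect and the primary ANCOVA are essentially untouched. The test should be fixed before analysis. The missing-data wording needs correcting whichever test is used.

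**What to change.** State in section 2.11 that the group-by-time interaction will be tested over a few prespecified phases: induction, pneumoperitoneum, release and, where recorded, PACU. This gives at most 3 df. Use T0 as a baseline covariate where it is measured (blood gases have no T0 value). Use a bias-corrected sandwich with an F reference on patient-based degrees of freedom; the true size is then about 5%.

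If all time points stay in the test, use a Hotelling-type F reference with denominator df N − p − 1. Bias correction with chi-square (about 48%) or with F(20,50) (about 35%) is not enough. A mixed model with unstructured covariance over 20 post-baseline points is not a realistic substitute, since it needs 20 × 21/2 = 210 covariance parameters from about 52 patients.

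In the missing-data paragraph, delete the label non-parametric and state that unweighted GEE on incomplete series is valid only if data are missing completely at random.

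The cost is a change of wording, with the same data and standard software. The downside is that the test describes minute-by-minute changes more coarsely; plots can still show every point.

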### Outcomes

2.6

The primary outcome of the study will be the time-weighted average (TWA)-MAP measured throughout anesthesia using an arterial line connected to a FloTrac™ sensor (Edwards Lifesciences, Irvine, CA, United States). For each participant, TWA-MAP will be calculated as the integral of MAP over elapsed time divided by the total observation duration, using the trapezoidal method. Data will be collected at approximately 1-min intervals when available, and measurements identified as technical artifacts (e.g., arterial line flushing, signal disconnection, damping artifacts, or recording errors) based on inspection of the arterial pressure waveform and corresponding clinical records will be excluded following data quality assessment. The primary analysis will compare TWA-MAP between the remimazolam and propofol groups to test the hypothesis that remimazolam-based TIVA will maintain a ≥20% higher intraoperative MAP than propofol-based TIVA.

Secondary outcomes will include the cumulative intraoperative burden of hypertension and hypotension. Hypertensive burden will be quantified as the area under the curve above the hypertension threshold (SBP ≥140 mmHg or MAP ≥100 mmHg), expressed in mmHg·min using the trapezoidal method. Hypotensive burden will be quantified as the area under the curve below the hypotension threshold (SBP <90 mmHg or MAP <65 mmHg), also expressed in mmHg·min. Group comparisons will assess whether remimazolam-based TIVA differs from propofol-based TIVA in hypertensive and hypotensive burdens. The time frame for secondary outcomes will extend from the start of induction to exit from the operating room.

In addition, intraoperative adverse hemodynamic events, including hypotension, hypertension, bradycardia, and tachycardia, will be recorded. Preoperative data will include patient characteristics, such as height, weight, age, diagnosis, scheduled surgical procedure, medical history, preoperative medication use, and baseline vital signs. Intraoperative data will include the surgical procedure performed, anesthesia duration, operative duration, degree of head-down tilt, vasopressin administration for bleeding control, estimated blood loss, fluid administration, and remifentanil dosage. Postoperative data will include post-anesthesia care unit (PACU) stay duration, PACU vital signs, and administration of additional medications, such as antiemetics and analgesics.

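### The only sensitivity analysis named for the primary TWA-MAP result, a GEE over T0–T43, targets a different quantity, so agreement or disagreement says little about the primary result

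*Protocol article*

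**What the plan says.** **Primary outcome.** Section 2.6 (Outcomes) states: "The primary outcome of the study will be the time-weighted average (TWA)-MAP measured throughout anesthesia". For each participant it is "calculated as the integral of MAP over elapsed time divided by the total observation duration, using the trapezoidal method", from readings about one minute apart. Section 2.11 (Statistical analysis) analyzes it by ANCOVA with six covariates (baseline MAP, age, BMI, ASA-PS, hypertension, diabetes) in the per-protocol set.

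**Sensitivity analysis.** Section 2.6 introduces serial measurements to be "assessed at prespecified time points to evaluate temporal changes and validate consistency with the primary outcome". The schedule is T0 before induction, T1–T10 each minute from the start of the induction drug, T20–T23 after positioning and pneumoperitoneum, T30 and T31 at and after release, "and upon PACU arrival (T40), followed by every 10 min for 30 min (T41–T43"). MAP is among the variables recorded in the PACU.

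Section 2.11 applies GEE to the repeated measures over T0–T43, MAP included, with group, time and group-by-time effects. The working correlation is to be chosen later. The same paragraph then gives the analysis its role: "As a sensitivity analysis, GEE analysis of serial blood pressure data will be performed to evaluate consistency with findings from the primary TWA-MAP analysis". No weighting by time is stated, and no contrast is named for comparison with TWA-MAP.

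**The concern.** A sensitivity analysis is informative when it estimates the same quantity under a changed assumption. TWA-MAP is an average over minutes of anesthesia. The serial model is built on a grid that is dense in the first 10 minutes, sparse afterwards, and includes points before and after anesthesia. Nothing is scheduled between T10 and T20 or between T23 and T30, so much of maintenance is unsampled.

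Two misreadings are then possible. A sound TWA-MAP result may look contradicted because the grid emphasizes induction or recovery, or a fragile one may look confirmed for the same reason. Section 3 (Discussion) makes this more than theoretical. It says earlier randomized trials concentrated largely on induction or on hypotension, and that a retrospective study in the Trendelenburg position found a different pattern. A group difference that changes between phases is therefore plausible here.

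The choices the primary result does depend on, namely the per-protocol set and the covariate list, are not specified to vary in this check.

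**Working it through.** The plan states no weights, so there is no figure of its own to reproduce. The check compares how each analysis weights time.

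**Step 1. Count the grid (section 2.6).**

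| Phase | Points | Count | Share of 21 |
|---|---|---|---|
| First 10 min | T1–T10 | 10 | 10/21 = 47.6% |
| Rest of anesthesia | T20–T23, T30, T31 | 6 | 6/21 = 28.6% |
| Outside anesthesia | T0, T40–T43 | 5 | 5/21 = 23.8% |

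**Step 2. Shares in TWA-MAP.** Anesthesia duration L is not given; 120–240 min is assumed. The first 10 minutes carry 10/L: 10/120 = 8.3%, 10/180 = 5.6%, 10/240 = 4.2%. PACU time carries 0%.

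**Step 3. Pooled group effect from the GEE.** With categorical time, complete data and one group coefficient, the estimate is a weighted mean of the 21 group differences. The weights are proportional to R⁻¹1, where R is the working correlation matrix.

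- *Independence or exchangeable:* all weights are equal, so the shares are those in Step 1.
- *AR(1) by visit order:* the two end points (T0, T43) have relative weight 1 and the 19 interior points 1 − ρ.
  - ρ = 0.3: total 2 + 19 × 0.7 = 15.3. First 10 min 7.0/15.3 = 46%; outside anesthesia (2 + 3 × 0.7)/15.3 = 27%.
  - ρ = 0.9: total 2 + 19 × 0.1 = 3.9. First 10 min 1.0/3.9 = 26%; outside (2 + 3 × 0.1)/3.9 = 59%.
- *AR(1) by clock time:* assumes T0 3 min before induction, T20 at 40 min, T30 and T31 at 25 and 15 min before the end, PACU arrival 5 min after the end, and correlation 0.80–0.95 per minute. First 10 min 12–16%; outside 37–43%.

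As the first-10-minute share falls, the outside share rises. No structure tried comes near 4–8% and 0%.

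**Step 4. What this could do, for a pooled effect with equal weights.** L = 180 min; no difference at T0 or in the PACU.

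| True group difference | TWA-MAP | Pooled GEE |
|---|---|---|
| 10 mmHg, first 10 min only | 10 × 10/180 = 0.6 | 10 × 10/21 = 4.8 |
| 10 mmHg, after 10 min only | 10 × 170/180 = 9.4 | 10 × 6/21 = 2.9 |
| +10 early, −3 afterwards | (100 − 510)/180 = −2.3 | (100 − 18)/21 = +3.9 |
| 7 mmHg throughout anesthesia | 7.0 | 7 × 16/21 = 5.3 |

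A GEE fitted to constructed data for the first two rows returned 4.76 and 2.86 under both independence and exchangeable correlation.

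**Step 5. With the group-by-time terms the plan specifies.** With T0 as reference, the group coefficient is the pre-treatment difference (0.0 in the constructed data). The interaction terms are separate differences at each point relative to T0. Neither is an estimate of TWA-MAP.

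**Step 6. Would dropping T0 and the PACU suffice?** No. Among the 16 points T1–T31, the first 10 minutes still hold 10/16 = 62.5%. Weighting by elapsed time is also needed.

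**The case against.** The best defense is that the plan never says the 21 points will be averaged. It includes group-by-time terms and leaves the correlation open. A difference confined to induction would then show as a difference at T1–T10 and none elsewhere, which is honest and useful. The declared aim is modest, to describe change over time and look for consistency, and a phase-by-phase picture reveals what a single average hides. An unseen analysis plan may fix the contrast and the correlation.

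Much of this stands. A reader might infer that the planned GEE gives half its weight to induction and a quarter to times outside anesthesia. The document does not support that as a fact about the plan: it holds only for a pooled effect under independence or exchangeable correlation with complete data. Nor is modelling T0 as an outcome an error in itself, since in a group-by-time model with T0 as reference the interactions are differences in change from baseline. The GEE also handles missing values differently from the primary analysis, so it is not an exact repeat of the same choices.

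What does not fall away is the label. The article itself fixes the grid, the model and the purpose, and twice assigns the model to checking consistency with the primary outcome. None of the outputs it describes estimates the primary quantity, whichever correlation is chosen.

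**Conclusion.** The point holds in a limited form. The one sensitivity analysis named for TWA-MAP does not target TWA-MAP, so its agreement would not confirm the primary result and its disagreement would not refute it. The point counts (10, 5 and 6 of 21) are exact. The 48%, 24% and 29% weights, and the mmHg figures, are conditional on a pooled effect with equal weights and complete data; the mmHg figures also assume a 180-min anesthetic and no difference outside anesthesia. The 4–8% share in TWA-MAP rests on an assumed duration of 120–240 min.

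A reader might go further and infer that the primary analysis is compromised. It is not: the TWA-MAP estimate, its type I error and the sample size do not depend on this model. The harm is possible misreading of a supportive analysis.

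**What to change.** 1. In sections 2.6 and 2.11, describe the T0–T43 GEE as a descriptive analysis of trajectories and remove the claim that it checks the primary result.
2. Name two sensitivity analyses on TWA-MAP itself:
   - the same ANCOVA on all randomized participants with available MAP data. Section 2.10 already continues outcome collection after discontinuation where feasible. The sentence in 2.11 ruling out an intention-to-treat analysis would need amending;
   - the ANCOVA with baseline MAP as the only covariate, which is also how the abstract describes the primary model.
3. If the serial model is kept as a check, restrict it to T1–T31, use T0 as a covariate, and prespecify the group contrast Σ wₖdₖ. Here dₖ is the group difference at point k and wₖ is the share of anesthesia time that point represents.

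Recomputing TWA-MAP with artifacts left in is not a useful addition, because line flushes and disconnections would enter the average as if they were pressure.

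**Cost.** Wording in two sections and a few extra model runs on data already collected. The weights in item 3 would be coarse, because a few points must stand for the unsampled interval between T23 and T30. That is a reason to prefer items 1 and 2.

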### Trial design, setting, and recruitment

2.1

This study is a prospective, single-center, randomized, single-blind, parallel-group superiority trial that will be conducted at CHA Ilsan Medical Center. In total, 58 patients undergoing robotic laparoscopic hysterectomy will be enrolled between October 2025 and October 2026. The Consolidated Standards of Reporting Trials (CONSORT) flowchart and study timeline are presented in Figure 1 and Supplementary Table S1. This protocol was developed in accordance with the Standard Protocol Items: Recommendations for Interventional Trials (SPIRIT) guidelines, and the trial will be reported according to the CONSORT 2025 statement.

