### Eligibility criteria

2.2

Eligible participants will be adult patients scheduled to undergo robotic laparoscopic hysterectomy under general anesthesia. Based on the inclusion criteria, patients aged 19–65 years, with a body mass index (BMI) of 18.5–35 kg/m^2^, and of American Society of Anesthesiologists Physical Status (ASA-PS) I or II will be included. The upper age limit of 65 years was selected because aging affects cardiovascular physiology and anesthetic pharmacodynamics, thereby reducing population heterogeneity (Doi et al., 2020). Similarly, the BMI range of 18.5–35 kg/m^2^ was chosen because extremes of body weight are associated with altered pharmacokinetic and pharmacodynamic characteristics that may influence hemodynamic responses to anesthetic agents (Park et al., 2018; Kim, 2021). Patients will be excluded if they present with preoperative systolic blood pressure (SBP) ≥ 160 mmHg or <90 mmHg, heart rate (HR) < 60 beats per minute or ≥100 beats per minute, hypoxemia defined as oxygen saturation (SpO_2_) < 90%, or a history of ischemic heart disease, cardiac conduction abnormalities, or severe respiratory disease, including uncontrolled asthma or chronic obstructive pulmonary disease. Additional exclusion criteria will include the administration of inhalational anesthetics during anesthesia and intraoperative conversion from robotic laparoscopic hysterectomy to open surgery.

This single-center trial will be conducted at CHA Ilsan Medical Center, a university-affiliated secondary hospital equipped with advanced robotic surgical platforms and electronic anesthesia documentation systems. All anesthesia will be administered by board-certified anesthesiologists with ≥3 years of clinical experience in total intravenous anesthesia using propofol and remimazolam infusion techniques. Participating surgeons will be experienced in robotic laparoscopic hysterectomy, each having performed >50 procedures before study initiation.

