### Harms and criteria for discontinuation or modification

2.5

Remimazolam and propofol are routinely used intravenous anesthetics for robotic laparoscopic surgery at our institution. Therefore, participation in our trial is not anticipated to introduce additional risk. However, hypotension and bradycardia may occur following administration of sedatives or opioids, and hypertension or tachycardia may arise in response to surgical stimuli. Hypotension (SBP <90 mmHg or MAP <65 mmHg) will be managed by reducing the remifentanil infusion rate. Severe hypotension (SBP <80 mmHg or MAP <60 mmHg) will be treated with intravenous ephedrine 5–10 mg or phenylephrine 30–100 μg. Hypertension (SBP >140 mmHg or MAP >100 mmHg) will be managed by increasing the remifentanil infusion rate, whereas severe hypertension (SBP >160 mmHg or MAP >105 mmHg) will be treated with intravenous nicardipine 300–500 μg or labetalol 5–10 mg. Bradycardia (HR < 45 beats/min) will be treated with intravenous glycopyrrolate 0.2 mg or atropine 0.25 mg, and tachycardia (HR > 100 beats/min) will be managed using intravenous esmolol 10–20 mg.

Study interventions may be modified or discontinued in cases of severe hypotension (SBP <80 mmHg or MAP <60 mmHg) unresponsive to protocol-directed vasopressor therapy, severe bradycardia (HR < 40 beats/min) unresponsive to atropine or glycopyrrolate, severe hypoxemia (SpO_2_ < 90% for more than 1 min), a severe allergic reaction to study medications, or if the attending anesthesiologist determines that continuation of the assigned intervention is unsafe. In such situations, anesthesia may be transitioned to an alternative regimen at the clinician’s discretion, and the event will be documented in the case report form (CRF).

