### Data management

2.10

All study data will be documented in standardized, paper-based CRFs developed for this trial. The CRFs will be pilot-tested in five patients before study initiation to ensure feasibility, clarity, and internal consistency. To maintain data quality, study personnel will receive pre-study training on CRF completion and data handling procedures. Duplicate checks of key variables (hemodynamic parameters and anesthetic drug doses) will be conducted, and 10% of completed CRFs will be randomly audited against source documents by an independent investigator. Any discrepancies will be resolved by consensus.

Intraoperative hemodynamic variables recorded using the Vital Recorder system will be extracted into a structured Excel file, which will serve as the source data. Relevant parameters, including MAP, HR, CO, CI, and SVV at each prespecified time point, will be transcribed into the CRF. The original Vital Recorder files will be archived as source documents linked to their corresponding CRFs.

To minimize missing data, participants will be observed continuously until discharge from the PACU. If a participant discontinues or deviates from the assigned intervention, outcome data will continue to be collected whenever feasible, including intraoperative hemodynamic variables, adverse events (hypotension, hypertension, bradycardia, and tachycardia), anesthetic drug doses, surgical characteristics, PACU duration, and postoperative vital signs. Reasons for non-adherence (e.g., conversion to inhalational anesthesia, conversion to open surgery, or discontinuation due to adverse events) and non-retention (withdrawal of consent or early termination) will be documented in the CRF. Participants who withdraw consent will be requested to permit use of data collected prior to withdrawal.

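### The primary analysis of this superiority trial is per-protocol, with exclusions after allocation that can depend on MAP itself, and no all-randomized analysis is planned

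*Protocol article*

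**What the plan says.** Section 2.1 describes a "prospective, single-center, randomized, single-blind, parallel-group superiority trial". Section 2.11 fixes the population: "The primary efficacy analysis will follow the per-protocol (PP) principle, including all randomized participants who fully adhere to the study protocol". It then rules out the alternative: "No intention-to-treat analysis is planned".

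The grounds for exclusion in section 2.11 are:
- major deviations, "such as conversion to open surgery, administration of inhalational anesthetics, incomplete intraoperative hemodynamic monitoring, or early withdrawal, will be excluded from the PP analysis";
- stopping for harm: "Participants who discontinue the intervention due to serious adverse events will also be excluded";
- more than 5% missing values on a continuous outcome, given in the missing-data paragraph.

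Section 2.2 places two of these events among the eligibility rules: "Additional exclusion criteria will include the administration of inhalational anesthetics during anesthesia and intraoperative conversion from robotic laparoscopic hysterectomy to open surgery".

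Section 2.5 says "Study interventions may be modified or discontinued in cases of severe hypotension" (SBP below 80 or MAP below 60 mmHg) that does not respond to vasopressors. It lists other triggers too, including the attending anesthesiologist's judgment that continuing is unsafe. Section 2.10 says that after discontinuation or deviation "outcome data will continue to be collected whenever feasible, including intraoperative hemodynamic variables". The only other population defined is a safety set of everyone dosed, analyzed by treatment received.

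**The concern.** A superiority claim rests on comparing groups that differ only by chance and by assigned treatment. Removing patients for what happens after allocation gives up that protection. Here the matter is sharper than usual, because one route out of the analysis runs through the primary outcome variable: a patient whose MAP stays very low can leave the MAP comparison for that reason. Section 1 says that propofol frequently causes hypotension and bradycardia, so the trial's own rationale makes it plausible that such exits differ between arms. Without an all-randomized result, a reader of the final report could not tell whether the exclusions mattered.

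**Working it through.** **Step 1. Timing of the exclusions.** Section 2.8 has the envelope opened immediately before induction. Open conversion, inhalational agent, incomplete intraoperative monitoring, stopping for a serious adverse event and more than 5% missing intraoperative values can only be known later, and early withdrawal here means withdrawal of a randomized participant. All are post-allocation exclusions, including the two listed as eligibility criteria in section 2.2.

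**Step 2. Link to the outcome.**

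| Section | Content |
|---|---|
| 2.5 | Refractory SBP <80 or MAP <60 mmHg may lead to discontinuation |
| 2.8, 2.9 | The anesthesiologist who decides knows the allocation |
| 2.12 | Severe hypotension is given as an example of a serious adverse event |
| 2.11 | Discontinuation for a serious adverse event means exclusion |
| 2.6 | The primary outcome is time-weighted average MAP |

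Read together, these allow a patient to be removed from the MAP analysis because of low MAP.

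**Step 3. Is there an as-randomized check elsewhere?** The GEE sensitivity analysis changes the method, and no all-randomized population is named for it. The safety set is analyzed as treated. Neither supplies one.

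**Step 4. The plan's planning figures (section 2.7).** The medians and quartiles are 81.3 [76.9–92.5] and 76.8 [67.8–82.5] mmHg. With mean = (q1 + median + q3)/3 and SD = (q3 − q1)/1.35:
- remimazolam: mean 250.7/3 = 83.57, SD 15.6/1.35 = 11.56;
- propofol: mean 227.1/3 = 75.70, SD 14.7/1.35 = 10.89;
- difference 7.87 mmHg, pooled SD √((11.56² + 10.89²)/2) = 11.23, d = 0.70, as stated.

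The dropout step also reproduces: 52/0.9 = 57.8, so 58, or 29 per arm. The 26 per group does not reproduce at two-sided 0.05 and 80% power (33.02, so 34, by the t-test); it matches a one-sided test (25.94). That is a separate issue, and the conclusion here does not depend on it.

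**Step 5. Illustrative shift (assumed exclusions).** If k of 29 propofol patients with average MAP m are dropped, the arm mean rises by k(75.7 − m)/(29 − k).

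| m (mmHg) | k = 2 | k = 3 |
|---|---|---|
| 60 | 2 × 15.7/27 = 1.16 | 3 × 15.7/26 = 1.81 |
| 65 | 2 × 10.7/27 = 0.79 | 3 × 10.7/26 = 1.23 |
| 70 | 2 × 5.7/27 = 0.42 | 3 × 5.7/26 = 0.66 |

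At m = 60 this is 1.16/7.87 = 15% and 1.81/7.87 = 23% of the planned difference.

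**Step 6. Simulation** (29 per arm, unadjusted two-sided t-test, 40,000 replicates, 1 to 4 patients dropped from the propofol arm only).

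| Dependence of exclusion on MAP | Shift in difference under no true effect (mmHg) | Type I error |
|---|---|---|
| None | about 0 | about 0.05 |
| Correlation 0.5 | −0.4 to −1.4 | 0.054 to 0.076 |
| Complete (lowest MAP dropped) | −0.8 to −2.7 | 0.066 to 0.173 |

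**Step 7. Power.** With the noncentral t, two-sided 0.05 and d = 0.70, power is 69.7% with 26 per arm and 74.5% with 29.

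**The case against.** The strongest reply is that the harmful route may rarely be used. Patients are ASA I–II, aged 19–65, with preoperative SBP limits. Hypotension must be refractory to vasopressors before it is a discontinuation trigger, and section 2.5 says only that treatment may then be modified or discontinued. Open conversion and incomplete monitoring need not be related to the drug, and surgeons are blinded. This all stands: it limits how much bias to expect, but it does not supply the missing analysis.

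The figures are also open to challenge. No document gives a rate of refractory hypotension, let alone in one arm only. An average near 60 mmHg over the whole anesthetic equals the severe-hypotension threshold, and a patient whose regimen is switched could average well above it; the rows for 65 and 70 mmHg show how the shift then falls. The illustrated bias shrinks the remimazolam advantage, so it works against the trial's hypothesis. The power gain is an upper bound, since withdrawals and failed monitoring cannot be recovered by redefining the population. These points stand as well.

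Three stronger readings are tempting but not supported:
- A reader might infer that excluded patients appear in no analysis. They can be in the safety population, and section 2.11 does not name the population for the secondary outcomes or the GEE models.
- A reader might infer that every patient with severe hypotension is removed. The text excludes those who discontinue because of a serious adverse event.
- A reader might infer that unblinded staff choose the per-protocol set. They decide on discontinuation; who assigns patients to the set is not stated, and section 2.9 sends the recorded data to a blinded investigator. That blinding cannot reverse a selection made earlier in the operating room.

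**Conclusion.** The point holds for the primary analysis. A self-described superiority trial tests time-weighted average MAP only in full adherers, expressly plans no intention-to-treat analysis, and lets some exclusions depend on MAP and on a decision by someone who knows the allocation. The primary comparison is therefore not protected by randomization, and the as-treated safety set does not fill the gap. This should be changed before any results are seen.

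The documents do not settle the size or direction of bias. The 1.2 to 1.8 mmHg shift rests on assumed exclusions of 2 or 3 propofol patients near 60 mmHg, with none on remimazolam, and omits the ANCOVA covariates; it is not a forecast. If low-MAP patients were excluded mainly from the remimazolam arm, the shift would reverse. If exclusion is unrelated to MAP, there is no bias, and the loss is at most the step from 74.5% to 69.7% power, assuming d stays at 0.70.

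**What to change.** - **Section 2.11, population.** Make the primary analysis the ANCOVA of time-weighted average MAP in all randomized participants who start induction, in the group assigned. Use all recorded MAP whether or not the regimen was switched, an inhalational agent was given or surgery was converted. Keep the per-protocol set as a supportive analysis. Delete "No intention-to-treat analysis is planned".
- **Section 2.11, missing data.** Confine the exclusion for more than 5% missing values to the per-protocol set. For the primary analysis, compute the average over the recorded time available and add a sensitivity analysis for missing data. Without this step the new primary population would have no missing-data rule of its own.
- **Section 2.2.** Delete the sentence that lists the two intraoperative events as exclusion criteria. Section 2.11 already lists both as major deviations, so nothing has to be moved.

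The cost is wording. No clinical rule changes, and section 2.10 already plans to keep collecting hemodynamic data after a deviation. There are two downsides: slight dilution from patients who switch regimen, and data after a deviation that will exist only where collection proves feasible.
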